
### Research Objectives:

To compare the effects of` oral iron (Iron III Hydroxide Polymaltose Complex eq. to Elemental Iron, 100 mg per day for three months) supplementation (Group-A) versus Intravenous (IV) iron (Ferric carboxymaltose 500 mg, three doses for three months) (Group-B) versus no treatment (Group-C) on serum ferritin level, four months post-intervention.To evaluate the change in the severity of clinical indicators of Hypoferritinemia without Anemia between Group A, B and C, four months post-intervention.

## METHODS

### Study Design:

This single-blinded, multicenter, multi-arm, randomized controlled trial (RCT) will employ a parallel assignment interventional model.

### Setting:

Participants will be recruited from four major tertiary care hospitals and surrounding communities in Lahore. A comprehensive list of government and private hospitals will be obtained from the Health Department of Punjab, sorted by bed capacity. The top two private and two government hospitals will be selected based on their number of beds.

### Sample Size:

The sample size will be calculated under the hypothesis that intravenous (IV) treatment will more effectively alleviate symptom scores compared to oral or no intervention after four months. Based on a 41.7% prevalence of HWA^16^ and an anticipated 45% reduction in prevalence post-intervention, a sample size of ninety-six patients per group is required, with a 5% inflation for loss to follow-up. Therefore, one hundred patients will be recruited in each of the three groups, totaling three hundred participants.

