## DISCUSSION

The literature reveals a significant gap in understanding various aspects of hypoferritinemia without anemia (HWA). Firstly, HWA is often underdiagnosed due to its nonspecific symptoms, which can overlap with other conditions. While there are estimates regarding the disease burden, precise figures are lacking, particularly in developing countries. Secondly, while extensive data exist on the causes of iron deficiency, there is a paucity of information on the determinants and causes of HWA specifically. Thirdly, management strategies for HWA are contentious; some researchers advocate for oral iron as the initial treatment, whereas others support intravenous (IV) therapy to alleviate symptoms more rapidly. This trial aims to evaluate the effectiveness of oral versus IV iron by comparing ferritin levels before and after treatment. In summary, there is limited evidence-based treatment available for the clinical symptoms associated with HWA, with many patients being prescribed antidepressants or analgesics instead of appropriate iron therapy. This study’s primary objective will be to raise awareness among clinicians about the importance of diagnosing HWA in patients presenting with relevant symptoms and to encourage the appropriate use of iron therapy (oral or intravenous) rather than relying on symptomatic treatments or misuse of drugs.

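### The stated calculation for 96 per group contains no assumption about the oral arm, so it does not show that the trial is powered for IV against oral iron

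*Protocol article*

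**What the plan says.** The Sample Size section gives one hypothesis with two comparators: "intravenous (IV) treatment will more effectively alleviate symptom scores compared to oral or no intervention after four months". It then gives one reference rate, one effect and one size: "Based on a 41.7% prevalence of HWA^16^ and an anticipated 45% reduction in prevalence post-intervention, a sample size of ninety-six patients per group is required". A 5% allowance for loss to follow-up leads to 100 recruited per group and 300 in total. Significance level, sidedness, power and formula are not stated, and no expected rate is given for the oral arm.

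Oral against IV iron is a central question elsewhere in the article. The Abstract's objectives begin with it, and the Discussion states: "This trial aims to evaluate the effectiveness of oral versus IV iron by comparing ferritin levels before and after treatment". Research Objectives sets oral iron "versus Intravenous (IV) iron (Ferric carboxymaltose 500 mg, three doses for three months) (Group-B) versus no treatment (Group-C) on serum ferritin level" without ranking the three pairwise comparisons.

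**The concern.** A sample size for IV iron against oral iron needs an assumption about what oral iron does. The section supplies none, yet its hypothesis names oral iron as a comparator. Group A is an active arm, taking 100 mg elemental iron daily for three months. If the single comparator rate is a prevalence left unchanged, the resulting size applies to IV against oral only if oral iron has no effect.

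Readers are therefore told that the size serves a comparison for which no calculation is shown. If Group B against Group A then turned out non-significant, there would be no stated basis for judging whether the trial could have found a difference worth having.

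**Working it through.** **Inputs from the Sample Size section.** Reference rate 0.417; reduction 45%; 96 per group; 100 per group recruited. The reduction must be relative, because a fall of 45 percentage points from 41.7% is impossible. So p(IV) = 0.417 × 0.55 = 0.229.

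**Assumptions, because the article is silent.** Two-sided 5% and 80% power, chosen because they reproduce 96. The oral effect is also assumed and is shown as a range.

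**Step 1: reproduce 96.** Two proportions, normal approximation, with p̄ the mean of the two rates:

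n = [1.96 √(2p̄(1−p̄)) + 0.842 √(p₁(1−p₁) + p₂(1−p₂))]² / (p₁−p₂)²

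With 0.417 and 0.229:
- pooled formula: 96.3 per group (97 rounded up)
- arcsine formula: 95.6 (96 rounded up)
- unpooled formula: 93.6 (94 rounded up)
- pooled formula at 90% power: 128.5, which does not fit

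The stated size therefore matches a two-group comparison of an unchanged 41.7% with 22.9%.

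**Step 2: apply the same basis to IV against oral.** Set p(oral) = 0.417 × (1 − r), p(IV) = 0.229 and n = 96 per group. Power = Φ{[|p₁−p₂|√n − 1.96 √(2p̄(1−p̄))] / √(p₁(1−p₁) + p₂(1−p₂))}.

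| Assumed oral reduction r | Oral rate | Power at 96 per group | n per group for 80% |
|---|---|---|---|
| 0% | 41.7% | 80% | 97 |
| 10% | 37.5% | 60% | 155 |
| 20% | 33.4% | 36% | 291 |
| 22.5% (half the IV effect) | 32.3% | 31% | 356 |

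Using all 100 per group changes little: 32% at half the IV effect.

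**Step 3: is the shortfall tied to 41.7%?** Inclusion Criteria require hemoglobin of at least 12 g/dl and ferritin below 30 ng/ml, so every participant has the condition at entry and the baseline is 100%. Keep the 45% reduction (IV at 55%) and 96 per group:

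| Assumed oral reduction | Oral rate | Power at 96 per group |
|---|---|---|
| 20% | 80% | 96% |
| 22.5% | 77.5% | 92% |
| 30% | 70% | 57% |

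The size of any shortfall thus depends on the reference rate as well as on the oral effect.

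**Step 4: what the enrolment can detect on the primary outcome.** Ferritin change is continuous and the article gives no SD, so the result can only be put in SD units.
- Detectable difference = (1.96 + 0.842) √(2/n): 0.40 SD with 100 per group, 0.41 SD with 95 (100 less 5%).
- 95% CI half-width = 1.96 √(2/n): 0.28 SD with either number.

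**The case against.** The strongest objection is that the unchanged comparator is inferred. The section never says that a comparator stays at 41.7%. The 45% could be read as before against after, or as the advantage of IV over whichever comparator is meant. If 96 already includes the 5% allowance, the base is about 91, and no two-sided 5%, 80%-power version of 41.7% against 22.9% was found to give that. This stands as a limit: the match to 96 is close but does not prove what was assumed about oral iron.

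Second, the power figures in Step 2 concern a prevalence that is neither the primary nor the secondary outcome, and the Statistical Analysis section lists no test of proportions. This also stands. A reader might infer that the trial is underpowered for IV against oral. The documents do not support that: power on ferritin change is unknown and may be adequate, and the prevalence shortfall largely disappears from a 100% baseline when oral iron has about half the IV effect.

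Third, a reader might infer that 96 is at least right for IV against no treatment. That is not supported either, since Group C also enters at 100%.

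Fourth, an article condenses a fuller protocol, where arm-specific rates may sit, and nothing in it says that a non-significant result would be read as equivalence. Both are fair, and the risk of misreading is only a risk. But the article does state the hypothesis and the inputs of its calculation, and as stated the inputs do not cover the hypothesis.

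**Conclusion.** The point holds in a limited form: the stated calculation does not show that the trial is powered for IV against oral iron, although its hypothesis says it serves that comparison. On the calculation's own basis, 80% power is reached only if oral iron does nothing; it falls to 60% with an assumed 10% oral reduction and to 31% at half the IV effect. This rests on an inferred 5% two-sided level, 80% power and an unchanged comparator, and on assumed oral effects. The percentages illustrate the gap in the stated basis. They are not the power of a planned analysis.

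**What to change.** In the Sample Size section:

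- Delete the claim that the calculation covers IV against oral iron. Do not re-label 96 as the size for IV against no treatment, because 41.7% does not describe Group C either.
- Keep 100 per group and state what it can detect for Group B against Group A on ferritin change: about 0.40 SD at 80% power and two-sided 5% (0.41 SD with 95 evaluable), or a 95% CI half-width of about 0.28 SD. If a ferritin SD is available, give these in ng/ml.
- State that Group B against Group A will be reported as a difference with its 95% CI, and that a non-significant result will not be read as equivalence.

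The cost is a few sentences and a less favourable stated basis for IV against oral. No patients, visits or tests are added.

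### The 100 per group in the sample-size paragraph covers about 4% loss to follow-up, not the stated 5%: a small rounding inconsistency of 1 to 2 women per group

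*Protocol article*

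**What the plan says.** The Sample Size paragraph of the protocol article gives three linked figures. It first sets the inputs: "Based on a 41.7% prevalence of HWA" and "an anticipated 45% reduction in prevalence post-intervention". It then states the result: "a sample size of ninety-six patients per group is required, with a 5% inflation for loss to follow-up". The next sentence draws the recruitment target from it: "Therefore, one hundred patients will be recruited in each of the three groups, totaling three hundred participants".

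The paragraph does not say whether 96 is the number before or after the allowance for loss. It gives no significance level, sidedness, power or formula. The abstract describes the total as approximately 300.

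**The concern.** The target of 100 is presented as following from 96 and a 5% allowance. Read that way, the three figures should agree, and they do not quite: taking 5% away from 100 gives a number below 96.

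What is at stake is the accuracy of a stated planning figure. When the trial reports, its actual attrition will be compared with the planned 5%, so the planned figure should be one that the target can absorb. The point concerns the attrition allowance only. It does not concern the choice of endpoint behind the 96.

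**Working it through.** **Inputs from the Sample Size paragraph:** 96 required per group; 5% allowance for loss; 100 recruited per group; baseline proportion 41.7%; 45% reduction.

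**Assumptions, because the article does not state them:** the 45% is a relative reduction, so the second proportion is 0.55 × 0.417 = 0.22935 (22.9%); two-sided 5% level (z = 1.960); 80% power (z = 0.842).

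**Step 1. Is 96 a figure before inflation?** The pooled two-proportion formula is

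n = [1.960 √(2p̄(1−p̄)) + 0.842 √(p1(1−p1) + p2(1−p2))]² / (p1−p2)²

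- With p1 = 0.417 and p2 = 0.22935: p̄ = 0.323175, 2p̄(1−p̄) = 0.43747, the sum of the two variances is 0.41986, and the difference is 0.18765. This gives n = 96.3.
- With p2 rounded to 0.229: n = 95.9.
- The arcsine formula with unrounded p2 gives 95.6.
- The unpooled formula gives 93.2 (rounded p2) to 93.6 (unrounded p2), so 94.

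The article's 96 is thus reproduced, before any allowance for loss, by a standard formula under common assumptions.

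**Step 2. Inflate 96 for 5% loss.**

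| Convention | Calculation | Per group | Total |
|---|---|---|---|
| Divide by (1 − 0.05) | 96/0.95 = 101.05 | 102 | 306 |
| Multiply by 1.05 | 96 × 1.05 = 100.8 | 101 | 303 |
| Stated in the article | – | 100 | 300 |

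The stated target is 1 to 2 per group, or 3 to 6 in total, below a full 5% inflation.

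**Step 3. What does 100 absorb?**

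- 100 × 0.95 = 95, one below 96.
- 100 − 96 = 4 women, which is 4.0% of those recruited.
- As an inflation factor, 100/96 = 1.042, or 4.2%.

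**Step 4. What does the difference cost?** Power from the formula in Step 1, with unrounded p2:

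| Completers per group | Power |
|---|---|
| 91 | 77.7% |
| 95 | 79.4% |
| 96 | 79.9% |
| 100 | 81.5% |

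Ending with 95 rather than 96 costs about 0.4 percentage points.

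**Step 5. The other reading.** If 96 already includes the 5%, the net requirement is 91: 91/0.95 = 95.8 and 91 × 1.05 = 95.6, and both round up to 96. On that reading 95 completers are more than enough, and 100 is simply 96 rounded up.

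**The case against.** Four points can be made on the other side.

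- **Most of the allowance is there.** Four of the 5 to 6 extra women per group are in the 100, and carrying 100.8 to a round 100 is ordinary rounding, the more so as the abstract calls the total approximate. This stands, and it sets the size of the point. A reader might infer that the allowance for loss was left out, but the figures do not support that.
- **The sentence is ambiguous.** The 5% may already sit inside the 96, and then there is no shortfall. This stands as a possibility. It is the less likely reading: it leaves the step from 96 to 100 without a stated reason, and the net figure of 91 gives about 78% power under the assumptions above, which is not a usual design target. Because the level, power and formula are unstated, the match in Step 1 supports the first reading but does not prove it. The pooled result of 96.3 would strictly round up to 97, and on the unpooled formula 95 completers exceed the need.
- **The effect on power is negligible.** This also stands. A reader might infer that the trial is underpowered at its planned loss. A change of 0.4 points does not support that; it is small beside the uncertainty in the inputs.
- **The 96 is not tied to the primary outcome.** It comes from a difference in proportions, while the primary outcome is change in serum ferritin. One completer more or fewer around 96 therefore says nothing about the power of the primary analysis. This is correct, and no such claim is made here.

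What the objection does not remove is that, on the natural reading, the three printed figures disagree. That is not a detail which a condensed article leaves to a fuller document.

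**Conclusion.** The point holds as a minor internal inconsistency. If 96 is the number required before inflation, which is the natural reading, then 100 per group allows for about 4% loss rather than 5%, and is 1 to 2 women per group short of a full 5% inflation. The comparison of 96, 5% and 100 needs no assumption beyond that reading. The cost of about 0.4 percentage points of power further assumes a relative 45% reduction, a two-sided 5% level and 80% target power. If the sponsor meant 96 to include the 5%, nothing is short, and the sentence only needs to say so. It is not a material sample-size error on either reading.

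**What to change.** Reword the one sentence under Sample Size, according to what was meant:

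- If 96 is the net requirement: *96 evaluable patients per group are required; 100 per group allows for 4% loss to follow-up.* Enrolment stays at 300.
- If 96 already includes the 5%: say so and give the net figure (about 91), with 100 described as a round-up.

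The cost is one sentence. Recruitment, budget and analysis do not change. If 96 is the net requirement, the stated allowance becomes slightly less generous.

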### Eligibility Criteria:

Eligible participants will be healthy females of reproductive age diagnosed with hypoferritinemia without anemia, with no comorbidities.

**Table-I T1:** Study Schedule.

Schedule of clinical assessments and procedures in the hospital						

In-hospital assessment	Visit 0	Visit 01	Visit 02	Visit 03	Visit 04	Visit 05
Informed consent	Yes					
Eligibility criteria	Yes	Yes				
Baseline data	Yes					
Blood sample	Yes	Yes				Yes
Randomize			Yes			
Give study medication			Yes	Yes	Yes	
Adverse event monitoring			Yes	Yes	Yes	
Post-intervention data						Yes

### Inclusion Criteria:

Females of reproductive age 18-45 years oldHaving iron deficiency symptoms such as fatigue/ laziness, poor productivity at work places, attention deficit and forgetfulness, sore tongue, dullness of skin and damage of nails, hair loss, prolonged wound healing and restlessness in legsHemoglobin higher than or equal to 12g/dlFerritin less than 30ng/ml in serumFemales with normal range of thyroid and blood sugar

### Exclusion Criteria:

Premature menopauseAnemia with hemoglobin <12 g/dl or abnormal CBC, Serum ferritin level >30, disturbed thyroid or blood sugar levelsHistory of iron or multivitamin consumption in the previous quarterPregnant or lactating femalesBlood transfusion or donation within the last three monthsComorbidities such as gluten intolerance, peri-anal vascular swelling, malignancies, urinary bleeding, cardiac and kidney failure, chronic gastritis, cirrhosis, or diabetesConcomitant Vitamin B12 or folic acid deficiencies, or inflammatory conditions affecting serum ferritin.

### Laboratory Tests:

***Complete Blood Count (CBC):*** All samples will undergo CBC to evaluate hematological parameters, including hemoglobin, red cell count, white cell count, platelet count, packed cell volume, mean cell volume, mean cell hemoglobin, mean cell hemoglobin concentration, and red cell distribution width, using an automated analyzer (Sysmex XN-1000, Tokyo, Japan).

***Serum Ferritin Concentration:*** A solid-phase sandwich assay using the streptavidin-biotin principle will be employed. Briefly, 96 wells will be covered with 200 µL of mouse anti-ferritin antibody. Serum samples, controls, and calibrators will be added in duplicate, followed by a conjugate working solution. After incubation and washing, TMB substrate will be added, and the optical density will be assessed at 450 nm with a microplate reader.

### Recruitment Strategy

### Participants will be recruited in three steps:

***Step-1:*** Purposive sampling of individuals who provide informed consent and meet the serum ferritin and hemoglobin criteria.

***Step-2:*** Screening based on inclusion and exclusion criteria, including blood tests for thyroid function and blood sugar.

***Step-3*:** Random assignment to groups A, B, or C via simple random sampling using a computer-generated list.

### Intervention:

***Group-A (n=100):*** Participants will receive oral iron supplementation (Iron III Hydroxide Polymaltose Complex, 100 mg) daily for three months, with compliance monitored through follow-up calls. Blood samples will be collected at the end of treatment period of four months.

***Group-B (n=100):*** Participants will receive IV iron supplementation (Ferric Carboxymaltose, 500 mg) once a month for three months. Blood samples will be collected at the end of treatment period of four months.

***Group-C (n=100):*** Participants will receive no treatment for three months. Blood samples will be collected at the end of treatment period of four months.

Randomized Controlled Trial Steps

### The trial will follow seven steps guided by the CONSORT guidelines:

***Recruitment of participants (Visit 0, Week 1):*** Study participants will be selected after signing the informed consent and meeting the eligibility criteria of the study. Blood sample for CBC and serum ferritin will be taken by the phlebotomist.

***Baseline data (Visit 0, Week 1):*** Baseline data will be recorded for eligible participants. The baseline data will include the socio-demographics information of the study participants and history of clinical symptoms of iron deficiency (pre intervention).

***Assessment of Eligibility (Visit 1, Week 1):*** Participants will be screened based on the results of CBC and serum ferritin. Blood samples of eligible participants will be collected for blood sugar and thyroid functions.

***Randomization (Visit 2, Week 2):*** Eligible participants with normal range of thyroid and blood sugar levels will be randomized to any of the three groups by using simple random sampling.

***Allocation (Visit 2, Week 2):*** After randomization, participants will be assigned to Groups A, B, or C, with specific intervention outlined.

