**Methods::**

We will choose a multicenter, multi-arm randomized controlled trial with a parallel assignment interventional model. About three hundred participants (n=300) aged 18-45 with hypoferritinemia without anemia and no comorbidities will be recruited. Participants will be randomized into three groups of one hundred each: Group-A will receive oral iron supplements (Iron III Hydroxide Polymaltose Complex, 100 mg elemental iron) one tablet per day for three months; Group-B will receive intravenous iron (Ferric carboxymaltose, one dose per month for three months); Group-C will receive no treatment. All groups will be followed for four months.

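### Simple randomisation is specified beside fixed groups of 100; the two do not agree as written, and balance across the four hospitals is left to chance

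*Protocol article*

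**What the plan says.** The allocation method is named twice. Recruitment Strategy, Step-3, reads: "Random assignment to groups A, B, or C via simple random sampling using a computer-generated list". The Randomization step (Visit 2, Week 2) says that eligible women "will be randomized to any of the three groups by using simple random sampling". Neither place mentions a block, a stratum or any other restriction.

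The group sizes are given as fixed numbers. The abstract's Methods paragraph says "Participants will be randomized into three groups of one hundred each". The Sample Size section states a requirement of 96 per group, adds 5% for loss to follow-up and concludes that "one hundred patients will be recruited in each of the three groups, totaling three hundred participants". The Intervention section repeats n=100 for each of Groups A, B and C.

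On sites, the Setting section says "Participants will be recruited from four major tertiary care hospitals and surrounding communities in Lahore", and then "The top two private and two government hospitals will be selected based on their number of beds". It gives no split of patients by hospital.

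**The concern.** In its usual sense, simple randomisation assigns each woman independently of the others. Group sizes are then random, and 100 per group is only the expected value. The article states the sizes as if the method produced them. A reader cannot tell whether the list is restricted, whether the sizes are expectations, or whether some unstated step brings the groups to 100.

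The design also deliberately mixes two private and two government hospitals. Nothing in the stated method keeps the three arms balanced within each hospital. If hospitals differ in starting ferritin, symptoms or follow-up, chance imbalance adds noise to the comparison that could easily have been avoided. Allocation cannot be repaired once it has happened, so the wording is worth settling beforehand.

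**Working it through.** **Inputs.** Total 300, ratio 1:1:1, 96 required per group, 5% loss, control rate "a 41.7% prevalence of HWA" and effect "an anticipated 45% reduction in prevalence post-intervention" (all Sample Size); four hospitals (Setting). Assumed because the article does not state them: two-sided alpha of 0.05, 80% power, the 45% read as a relative reduction, and 75 women per hospital.

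**1. The article's own figure.** p1 = 0.417 and p2 = 0.417 × 0.55 = 0.229, with mean 0.323. The usual two-proportion formula with pooled variance, no continuity correction, is

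n = [1.96·√(2·0.323·0.677) + 0.842·√(0.417·0.583 + 0.229·0.771)]² / (0.417 − 0.229)² = 96.3, which rounds up to 97.

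The unpooled form gives 94. The stated 96 is therefore reproduced closely. For loss, 96 × 1.05 = 100.8 and 96 / 0.95 = 101.1, close to the stated 100.

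**2. Group sizes under unrestricted 1:1:1 allocation of 300.**
- Standard deviation of one group: √(300 × 1/3 × 2/3) = 8.16. The 95% range is 100 ± 1.96 × 8.16, about 84 to 116.
- Probability of exactly 100/100/100: 300! / (100!)³ / 3³⁰⁰ = 0.00275, or 0.28%.
- From 1,000,000 simulated allocations: the median size of the smallest group is 92; the smallest group is below 96 in 78% of trials, so all three reach 96 in 22%; the largest and smallest groups differ by 20 or more in 35%.

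**3. Effect on power.** For A against B with the proportions above, power is 81.5% at 100 v 100. Averaged over the simulated sizes it is 81.2%, a loss of about 0.3 points; the 2.5th percentile is 77.8%. The mean variance inflation is 0.7%.

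**4. Balance within hospitals (75 each, assumed).**
- Unrestricted allocation: the standard deviation of one arm is √(75 × 2/9) = 4.08, so the 95% range is about 17 to 33 around 25. The median gap between the largest and smallest arm in the worst of the four hospitals is 13, and that gap is 10 or more in 84% of trials.
- Drawing 100 per arm without replacement from 300, ignoring hospital: the totals are exact, but the median worst-hospital gap is still 11.

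**5. Permuted blocks of mixed size 3, 6 and 9, within four hospitals, total 300.** Simulated with random hospital totals, expected shares either equal or 40/30/20/10%:
- exactly 100/100/100 in about 16% of trials, because each hospital can end on an incomplete block;
- all arms between 98 and 102 in about 95%;
- every arm at 96 or more in over 99.9%;
- median worst-hospital gap between arms of 2, never above 3.

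**6. Predictability of blocks.** With a known fixed block size and visible past allocations, the share of assignments fully determined is 33% (blocks of 3), 20% (blocks of 6) or 14% (blocks of 9). The best-guess hit rate is 61%, 56% or 53%, against 33% under simple randomisation.

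**The case against.** The strongest reply is that the 0.28% depends on one reading. Simple random sampling is a survey term. Beside a computer-generated list and three groups of one hundred, it could mean a prepared list with 100 places per arm, drawn without replacement, which gives 100 each every time. This stands as a possible reading. The article does not state it, however, and it does nothing for balance by hospital.

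The second reply is that unrestricted allocation is the least predictable scheme. That is a real merit here, because tablets, infusions and no treatment are visible to those who deliver them. This also stands. Blocks carry a cost, and small fixed blocks would be a poor choice.

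Third, stratification and block details are often left to a full protocol, and model terms to an analysis plan, neither of which is shown. That would answer a complaint about silence. It does not answer this one, since both the method and the sizes are stated, and they do not fit together as worded. Hospital in the analysis is proposed only as the companion to stratifying; its absence from the article is not held against the plan.

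Finally, nothing in the article shows that private and government patients differ, or that staff would close an arm once it reached 100. Both are fair points. The second is conjecture and no part of the conclusion.

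**Conclusion.** The stated method and the stated sizes are inconsistent as written. On the unrestricted reading the sizes would be met exactly in 0.3% of trials, and at least one arm would fall below 96 in about 78%. On the without-replacement reading the sizes are met, but the text needs to say so. On both readings hospital balance is left to chance.

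The consequence is modest, and three stronger conclusions that a reader might draw are not supported:
- **That the trial is underpowered because of this.** The average loss is about 0.3 points.
- **That the comparison is biased.** Chance imbalance under valid randomisation is not bias, and the article gives no figure for differences between hospitals.
- **That stratified blocks would deliver exactly 100 per arm at no cost.** They come close, reach exactly 100 each in only about 16% of trials, and bring some predictability.

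The power figure rests on an assumed two-sided 0.05 test and a relative reading of the 45% reduction. The within-hospital figures for the stated method rest on an assumed 75 women per hospital. The total-size figures for unrestricted allocation need only the 300 and the 1:1:1 ratio.

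**What to change.** In Recruitment Strategy, Step-3, and in the Randomization step, replace simple random sampling with a central, concealed, computer-generated list in permuted blocks of undisclosed, randomly varying size (for example 3, 6 and 9), stratified by hospital. Include hospital as a factor in the primary analysis. In the abstract, Sample Size and Intervention sections, give 100 per group as the target; arms will typically be 98 to 102.

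If the authors keep a simple scheme, the least they should do is state whether the list is unrestricted, with 100 as an expected size, or drawn without replacement with 100 places per arm. That removes the inconsistency but not the hospital imbalance.

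Before allocation starts, the change costs a different list and a few words. The downside is some end-of-block predictability, because arms are visible to treating staff. Central concealment and undisclosed, varying block sizes limit it but do not remove it.
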